## Number of Patients

This study will enroll a total of 24 patients with 12 patients in each study arm.

## Number of Study Centers

This will be a single-center trial run at the University of Utah Hospital.

## Study Duration

Study therapy will be a total of 9 weeks duration (with 8-week MBSR curriculum) and patients will be followed for 6 months (180 days) after completion of the study intervention. There will be a total of two groups of 12 subjects per study arm. Total duration for the study will be approximately one year.

# ELIGIBILITY CRITERIA

Potential study participants must meet all inclusion criteria and no exclusion criteria to be deemed eligible for trial participation. To ensure subject safety, all patients must be deemed eligible at the time of study registration and must continue to meet eligibility criteria up to the first group therapy session. This eligibility checklist is used to determine subject eligibility and will be filed with the enrolling investigator’s signature in the subject research chart.

**Subject No. ______________________**

**Subject’s Initials: (L,F,M) _________________**

## Inclusion Criteria

___ Participants must be physicians or nurses with at least 1 month of frontline clinical experience during the COVID pandemic.

**Yes/No Eligibility Questions (Response of “no” = subject ineligible)**

- PHQ-9 score ≥ 10 and meet DSM-5 criteria for a depressive disorder, including adjustment disorder with depressed mood.
- Meet our working definition of burnout which will involve a score on the emotional exhaustion subscale (≥ 27) and a ‘high’ score on one other subscale (either depersonalization ≥ 13 or personal accomplishment ≤ 21).
- Not taking regularly scheduled medications to treat depression and/or anxiety, including benzodiazepines, for at least 4 weeks prior to administration of psilocybin, if randomized to that study arm.
- Fluent in English.
- Reading literacy and comprehension sufficient for understanding the consent form and study questionnaires, as evaluated by study staff obtaining consent.
- Able to provide informed consent and willing to sign an approved consent form that conforms to federal and institutional guidelines.
- ECOG Performance Status ≤ 2.
- Have a support person that would be able to escort the subject home on the evening of the psilocybin dosing session. The use of ride services will not be permitted (e.g., Uber, Lift, taxi, etc.)
- (If randomized to psilocybin arm) Adequate liver function as defined as:
  - Total Bilirubin < 1.5x institutional upper limit of normal (ULN) unless elevated bilirubin is related to Gilbert’s Syndrome.
  - AST(SGOT)/ALT(SGPT) <3 x institutional ULN
  - For female subjects: Negative pregnancy test and agreement to use highly effective contraception or evidence of post-menopausal status if randomized to psilocybin arm. The post-menopausal status will be defined as having been amenorrheic for 12 months without an alternative medical cause.
  - For male subjects: agree to condom use during intercourse for 24 hours post-psilocybin dose.
  - Agree to refrain from using any psychoactive drugs, including alcoholic beverages, ondansetron, cannabis, and non-routine PRN medications within 24 hours of the psilocybin administration. Exceptions include daily use of caffeine, nicotine, and opioid pain medication.
  - Agree that for one week preceding the psilocybin session, he/she will refrain from taking any nonprescription medication, nutritional supplement, or herbal supplement except when approved by the research team. Exceptions will be evaluated by the research team and will include acetaminophen, non-steroidal anti-inflammatory drugs, and common doses of vitamins and minerals.
  - Agree not to use nicotine for at least 2 hours before the psilocybin administration and for the duration of the psilocybin session.
  - Agree to consume approximately the same amount of caffeine-containing beverage (e.g., coffee, tea) that he/she consumes on a usual morning, before arriving at the research unit on the morning of the psilocybin session. If the subject does not routinely consume caffeinated beverages, he or she must agree not to do so on the day of psilocybin administration.
  - Subjects requiring opioid use for pain are on a stable pain management regimen. Long-acting opioid medications (e.g., oxycodone sustained-release, morphine sustained release) will be allowed if the last dose occurred at least 6 hours before psilocybin administration; such medication will not be taken again until at least 6 hours after psilocybin administration.

## Exclusion Criteria

**Yes/No Eligibility Questions (Response of “yes” = subject ineligible)**

- Prior systemic antidepressants, antipsychotic, or anxiolytic medication within four weeks prior to administration of psilocybin (if randomized to psilocybin arm).
- Personal history or first- or second-degree relatives with schizophrenia, bipolar affective disorder, delusional disorder, schizoaffective disorder, psychosis, or other psychotic spectrum illness as determined by patient report and chart review.
- Current or history within the last two years of meeting DSM-V criteria of substance use disorder (excluding caffeine and nicotine). Current substance use disorders may be identified through the drug urine screening test as determined by patient report and chart review.
- Currently meeting DSM-V criteria for Dissociative Disorder, or other psychiatric conditions judged to be incompatible with the establishment of rapport or safe exposure to psilocybin as determined by patient report and chart review.
- Currently meeting DSM-V criteria for Cluster B Personality Disorder as determined by patient report and chart review.
- Severe depression requiring immediate standard-of-care treatment (e.g., hospitalization).
- Suicidal ideation over the past month as assessed as a yes to question 3, 4, or 5 on the Columbia-Suicide Severity Rating Scale, Suicidal Ideation section
- Cancer with known CNS involvement, previously treated brain metastasis, or other major CNS disease.
- Employment as house staff/residents
- The subject has uncontrolled significant intercurrent or recent illness including, but not limited to, the following conditions:
- Cardiovascular disorders: Congestive heart failure, including all New York Heart Association Classes.
- Angina pectoris, cardiac hypertrophy, cardiac ischemia, myocardial infarction
- Uncontrolled hypertension at the time of enrollment (BP>140 systolic or 90 diastolic), coronary artery disease, artificial heart valve
- Prolonged or congenital long QT syndrome (>450 ms), serious cardiac arrhythmias, tachycardia, a clinically significant screening ECG abnormality
- Renal insufficiency as defined as creatinine clearance < 40 mL/min calculated by Cockcroft-Gault formula
- Hepatic disorders: Active infection including hepatitis B (known positive HBV surface antigen (HBsAg) result) or hepatitis C.
- Any other condition that would, in the investigator’s judgment, contraindicate the subject’s participation in the clinical study due to safety concerns or compliance with clinical study procedures (e.g., infection/inflammation, intestinal obstruction, unable to swallow medication, [patients may not receive the drug through a feeding tube], social/ psychological issues, etc.)
- Known prior severe hypersensitivity to investigational product or any component in its formulations (NCI CTCAE v5.0 Grade > 3).
- Subjects taking prohibited medications. A washout period of prohibited medications for a period of at least five half-lives should occur prior to psilocybin administration.

**I certify that this subject meets all inclusion and exclusion criteria for enrollment in this study.**

**______________________________ ____________ ___________**

**Investigator Signature Date Time**

## Recruitment Strategies

Potential participants will be recruited from within the University of Utah Healthcare System through internal advertisements, flyers, and through the University of Utah Resiliency Center. If recruitment through internal sources proves challenging, we will expand our efforts to a 25-mile radius from University of Utah Hospitals and Clinics.

# TREATMENT PLAN

## Treatment Schedule

### MBSR Arm

Participants randomized to the MBSR only arm will be enrolled in the MBSR curriculum led by [name] LCSW through the University of Utah Resiliency Center. Cost for University of Utah employees ($99) will be covered through the study. If capacity limits the feasibility of running this internally we will consider utilizing MBSR groups through Intermountain as well as Davis Behavioral Health and this cost ($250 per participant) will be covered through the study. Mindfulness-Based Stress Reduction, (MBSR), was developed by Jon Kabat-Zinn at the Center for Mindfulness, University of Massachusetts Medical School. MBSR is an intensive training in developing mindful awareness and accessing our innate capacity for health, healing and growth. Groups meet for an orientation, 9 weekly classes and an all-day retreat held in the final two weeks of the curriculum Guided instruction in various practices is provided, including sitting and walking meditation, body scan, gentle yoga, and mindful communication. These practices are enhanced through inquiry exercises, group dialogue, and daily home assignments.

MBSR has been shown to be an effective ameliorative measure for healthcare related burnout (Cohen-Katz, 2005) independent of PAP. Given this, we believe it will be an ideal active comparator to the novel administration of psilocybin in this population.

### MBSR+PAP Arm

Participants randomized to the MBSR + PAP arm will participate in the same curriculum as described above, however, will substitute a group PAP session instead of the group MBSR retreat. The PAP intervention will be facilitated with a 1:1 therapist/participant ratio with an additional lead therapist. Group size will be determined by ease of recruitment but will be no fewer than 2, and no more than 6 participants per PAP session. The group will be overseen by a lead therapist who will be available through the entirety of the dosing session and will not be assigned to any one individual participant. Timing of the PAP session will be during the MBSR curriculum with a goal of scheduling at same time as the MBSR retreat for the other arm. However, scheduling will be flexible depending on participant schedules, particularly given working demands of healthcare providers amid a pandemic: this session may occur before or after the group meditation retreat +/- 1 week. The psilocybin session will be accompanied by 3 preceding group preparatory sessions of 90 minutes each (one of these can be via Zoom per participant) as well as 3 integration sessions of 90 minutes each (up to two of these can be via Zoom per participant). Participants must continue to meet all inclusion criteria as well as hepatic and renal function requirements laid out in inclusion and exclusion criteria to receive psilocybin.

#### Preparatory Sessions

All Preparatory Sessions are group based and approximately 90 minutes duration. They will cover the following topics: establishing safety and boundaries, an introduction of set/setting, description of psilocybin effects, rules of conduct during psilocybin session, and how to handle strong emotions. Up to 1 one of these preparatory sessions can be done remotely via Zoom per participant. Preparatory materials will be buttressed with education materials provided via the Storyline platform.

General supportive-expressive group goals will be followed, including a focus on building rapport and trust with the therapist team, expressing emotions, exploring work related stressors and symptoms of burnout and depression, exploring traumatic work-related events or issues, examining life priorities, and utilizing the support of family and friends.

#### The Psilocybin Session

The psilocybin medication session will occur in a group space in HMHI. This space will have accessibility to a restroom, a private break-out room (to be used as needed), and the HMHI pharmacy. Code Blue response is available within the facility. There will be a 1:1 ratio of therapists to participants present as well as a lead therapist not specifically assigned to any one participant. The room will have a chair for the individual therapists to sit near the subject to offer support and guidance. Participants will be seated in individual “stations” but will be within visual and auditory reach of those in their cohort. There will be a more private space available if the lead therapist and individual therapist deem an individual as needing it, mostly in a scenario in which loud speaking, crying or other behavior becomes disruptive to the group. Video recording equipment will be present throughout the duration of the session and will be part of the consenting process. Participants will be given specific reminders regarding the process for using the restroom or having a light snack. Participants will remain on-site with their therapist team for eight hours after administration of psilocybin and will have arranged transportation from the study site at the end of the day.

Prior to leaving the site at the end of the psilocybin dosing day each participant will be assessed by the lead study monitor ([name] MD or [name] MD) regarding safety to leave. This evaluation will consist of a medical screen for any concerning symptoms, a psychiatric screen for acute suicidality or significant emotional distress, and a cognitive screen assessing orientation. If there are clinical concerns that a given participant is not safe to leave the site along medical, psychiatric, or cognitive assessments the lead study monitor (one of the PIs) and the Lead Therapist will remain on site for ongoing assessment and support until the participant is deemed safe to depart with a designated ride and support person. If a given participant remains unsafe to leave the site despite ongoing assessment and support they will be escorted to either the HMHI Receiving Center (for psychiatric assessment and care) or the University of Utah Emergency Department depending on either psychiatric or medical clinical presentation.

#### Integration Sessions

Three group integration sessions will occur after the Psilocybin Session with the first occurring within 48 hours of the Psilocybin Session. Integration sessions will be 90 minutes in duration and participants may join up to two of these sessions remotely via Zoom at the clinical judgement of the study therapists and study team if there are scheduling difficulties. This material will also be buttressed by specific integration exercises through the Storyline platform. Focus of these sessions includes processing material that arose during the psilocybin session, examining emotional responses to this material, review of significance of this material in light of symptoms of depression and burnout, reflection on how to integrate this material into the workplace and personal life following the psilocybin session, practices to continue integrating this experience moving forward.

## Psilocybin

### Methods of Supply, Storage, Packaging, and Labeling

Usona Institute will provide psilocybin as 25mg capsules that will be packaged individually into high-density polyethylene bottles (30 cc). Bottles will be maintained at room temperature in a locked, secure location within the Investigational Drug Services Pharmacy at Huntsman Cancer Institute and in accordance with the Drug Enforcement Agency (DEA) regulations. Study staff with access to the psilocybin inventory will be pre-defined.

Once IP is prepared for dispense by the IDS pharmacy, the assigned treatment will be picked up from the IDS pharmacy by a study team member.  The individual who is picking up must be part of the research team and holding a Schedule 1 DEA license. No other individuals will be allowed to pick-up and transport the study drug to the study site. A chain of custody form and a medication pick-up log will be completed by both an IDS staff member and the research team member picking up the drug.

### Preparation and Administration

The Investigational Drug Services pharmacy at Huntsman Cancer Institute will prepare and dispense all investigational supplies. A designated study team member with a Schedule 1 DEA license will be responsible for transporting the study drug to the study site at HMHI. Appropriate records will be kept to accurately show all dispensing activates including the return of any unused Investigational Product (IP). IP will be supplied only to subjects deemed eligible for study therapy. IP may not be dispensed to patients who have not been enrolled in the trial.

Patients will be advised to refrain from the following for 24 hours before psilocybin:

- Cannabis
- Alcoholic beverages
- Psychoactive drugs
- Ondansetron
- Non-routine PRN medications

On the day of psilocybin administration, patients on opioids should not take any long-acting opioids within 6 hours prior to or 6 hours proceeding psilocybin administration. Patients should consume approximately the same amount of caffeine-containing beverage (e.g., coffee, tea) that he/she consumes on a usual morning, before arriving at the research unit. If the subject does not routinely consume caffeinated beverages, he or she must agree not to do so on the day of psilocybin administration. Patients should also not use nicotine for at least 2 hours before psilocybin administration.

All doses of psilocybin will be administered at the investigational site by qualified medical staff. The time of administration will be recorded in the patients’ research charts. Any reason for deviation from the protocol-specified dose or schedule will be documented in the subject’s research chart.

### Accountability and Compliance

The Investigational Drug Services Pharmacy at Huntsman Cancer Institute and the HMHI Pharmacy will maintain appropriate documentation of the receipt, dispensing, return, transportation, and destruction of all investigational product. All inventory tracking will be completed in duplicate by IDS pharmacy staff. A log will be maintained of all individuals with access to the IP and its storage location in a securely locked safe. Any theft or significant loss of IP will be reported to the DEA on DEA Form 106 within one business day of first knowledge in accordance with 21 CRF Part 1301.

Study drug will be properly stored in accordance with Drug Enforcement Agency requirements in the Investigational Drug Service Pharmacy and administered to registered study participants at Hunstman Mental Health Institute.

Once IP is prepared for dispense by the IDS pharmacy, the assigned treatment will be picked up from the IDS pharmacy by a study team member with a DEA Schedule I license.  The individual who is picking up must be part of the research team. No other individuals will be allowed to pick-up and transport the study drug to the study site. A chain of custody form and a medication pick-up log will be completed by both an IDS staff member and the research team member picking up the drug.

## Concomitant Medications and Therapies

### Supportive Care

All supportive measures consistent with optimal subject care may be given throughout the study. Patients will be encouraged to have a supportive care relationship with the social worker on their treatment team throughout the duration of the study and will be encouraged to maintain this therapeutic relationship with their social worker following completion of the study.

### Prohibited Therapy

Medications or vaccinations specifically prohibited in the exclusion criteria are not allowed during the active treatment period. Patients are prohibited from receiving the following therapies during the treatment phase of this trial if randomized to the psilocybin arm:

- Other investigational agents
- Herbal remedies known to potentially interfere with major organ function (e.g., hypericin)
- Monoamine oxidase inhibitors
- Medications known to be uridine diphosphate glucuronosyltransferase enzyme modulators
- Selective serotonin reuptake inhibitor/serotonin-norepinephrine reuptake inhibitors (SSRI/SNRI)
- Serotonin 5HT2A receptor antagonist
- Benzodiazepines
- First and second-generation antipsychotics
- St. John’s Wort

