| Diagnosis and Main Eligibility Criteria | **Key Inclusion Criteria:**   - Male or female healthcare providers aged ≥ 25 years old. - Participants must be physicians or nurses with at least 1 month of frontline clinical experience during the COVID-19 pandemic. - Screening MBI-HSS (MP) score that meets our working definition of burnout (emotional exhaustion subscale ≥ 27) and a ‘high’ score on one other subscale (either depersonalization ≥ 13 or personal accomplishment ≤ 21). - PHQ-9 depression screen ≥ 10. - Not taking regularly scheduled medications to treat depression and/or anxiety, including benzodiazepines, for at least 4 weeks prior to initiation of the study.   **Key Exclusion Criteria:**   - Prior systemic antidepressants, anti-psychotic, or anxiolytic medication within four weeks prior to psilocybin administration. - Personal history or immediate family members with schizophrenia, bipolar affective disorder, delusional disorder, schizoaffective disorder, psychosis, dementia, or other psychotic spectrum illness. - Currently meeting DSM-5 criteria for Dissociative Disorder, or other psychiatric conditions judged to be incompatible with the establishment of rapport or safe exposure to psilocybin. - Currently meeting DSM-5 criteria for Cluster B Personality Disorder). - Current or history within the last two years of meeting DSM-5 criteria of substance use disorder (excluding caffeine and nicotine). |
| Study Product, Dose, Route, Regimen | Psilocybin 25 mg PO |
| Duration of administration | One-time administration |
| Reference therapy | MBSR |
| Statistical Methodology | Feasibility will be assessed by the ability to recruit, consent, and enroll 24 patients in the trial, and for at least 16/24 patients to remain in the study until completion.  The key secondary analysis of QIDS-SR-16 and MBI-HSS(MP) will use mixed-effects models with fixed effects for time (enrollment, 2 weeks post psilocybin), and a random intercept term. The outcome variables are the estimated change from baseline to 2 weeks post psilocybin from these models. |

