### Assess the preliminary efficacy of MBSR+PAP vs MBSR alone in reducing symptoms of depression (as measured by the QIDS-SR-16).

*Primary Endpoint:* Efficacy will be assessed through mean reduction in QIDS-SR-16 scores at 2-weeks post intervention with between-group comparison. To understand longitudinal effects, we will gather data to 6 months post intervention for both arms. Participants will be screened for eligibility with the PHQ-9 with a cut-off score of ≥ 10 required for enrollment and participants must meet DSM-5 criteria for a depressive disorder (including adjustment disorder with depressed mood).

*Primary Endpoint:* The change in depression scores as measured by the QIDS-SR-16 from enrollment to 26 weeks post-completion of the intervention (MBSR curriculum).

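### The medication rules contradict each other and differ by arm, so entry cannot be settled before randomisation and a QIDS-SR-16 difference cannot be credited to PAP alone

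*Protocol*

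**What the plan says.** **Entry.** The key inclusion criteria in the Study Summary cover everyone: "Not taking regularly scheduled medications to treat depression and/or anxiety, including benzodiazepines, for at least 4 weeks prior to initiation of the study". Section 5.1 has the same criterion with a different scope and anchor: "for at least 4 weeks prior to administration of psilocybin, if randomized to that study arm". The matching exclusion in Section 5.2 reads: "Prior systemic antidepressants, antipsychotic, or anxiolytic medication within four weeks prior to administration of psilocybin (if randomized to psilocybin arm". Section 5.2 ends by excluding people on prohibited medications and adds: "A washout period of prohibited medications for a period of at least five half-lives should occur prior to psilocybin administration".

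**During treatment.** Section 6.3 (Prohibited Therapy) opens without an arm limit: "Medications or vaccinations specifically prohibited in the exclusion criteria are not allowed during the active treatment period". The list that follows covers SSRI/SNRIs, MAOIs, benzodiazepines, antipsychotics and other investigational agents, among others. It is introduced by: "Patients are prohibited from receiving the following therapies during the treatment phase of this trial if randomized to the psilocybin arm".

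**Comparison affected.** Section 1.1 assesses efficacy by "mean reduction in QIDS-SR-16 scores at 2-weeks post intervention with between-group comparison". The trial is open label with 12 participants per arm (Sections 4.2 and 9.2).

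**The concern.** Every participant has a depressive disorder, and the efficacy question is what PAP adds to MBSR on a depression score. If one arm may use antidepressants or anxiolytics and the other may not, the arms differ in drug treatment as well as in PAP. Randomisation balances what exists at assignment. It does not protect against differences that the protocol's own rules create afterwards, and in an open-label trial participants act on those rules knowing their arm.

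There is also a practical problem at entry. A candidate on a stable antidepressant is ineligible under the Study Summary, but acceptable under Sections 5.1 and 5.2 if allocated to MBSR. A site cannot follow both.

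**Working it through.** **1. The rules side by side**

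| Place | Applies to | Counted from |
| --- | --- | --- |
| Study Summary, key inclusion | everyone | 4 weeks before study start |
| Study Summary, key exclusion | no arm stated | 4 weeks before psilocybin |
| Section 5.1 | psilocybin arm | 4 weeks before psilocybin |
| Section 5.2, antidepressant item | psilocybin arm | 4 weeks before psilocybin |
| Section 5.2, washout item | no arm stated | five half-lives before psilocybin |
| Section 6.3, list | psilocybin arm | treatment phase |

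**2. Can the criterion be assessed when it must be?** Section 5 requires eligibility at registration, Section 13 requires all criteria to be met before registration, and Section 9.2 randomises people who already meet them. A criterion that applies only after a given allocation cannot be checked in that order. Its look-back window also lies after screening, as step 3 shows.

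**3. Timing.** In Table 2, week 3 is days 15-21, so week 7, the PAP session, is days 43-49.

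- Four weeks before dosing: 43 − 28 = 15 and 49 − 28 = 21, so the window opens on days 15-21.
- Section 6.1 lets the PAP session move by one week either way, to days 36-56. The window then opens on days 8-28.
- Screening ends at day −7. The baseline QIDS-SR-16 is taken in week 1, before the first MBSR session.

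Read alone, Sections 5.1 and 5.2 would therefore let a psilocybin-arm participant stop a drug after baseline. Table 2 labels weeks 1-9 as active, however. If that is the treatment phase of Section 6.3, the same drugs are barred from week 1. The two rules disagree on when the psilocybin arm must be drug-free.

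**4. Does any other text bind the MBSR arm during treatment?** The opening sentence of Section 6.3 imports the exclusion criteria, but the antidepressant and anxiolytic exclusion there is limited to the psilocybin arm. The washout item relies on the prohibited list and is tied to psilocybin administration. The Study Summary criterion has no arm limit but concerns entry only. Nothing clearly restricts these drugs in the MBSR arm once treatment starts.

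**5. Analysis.** The model in Section 12.2 has terms for treatment, time, their interaction and participant, and none for co-medication. Table 2 schedules concomitant-medication assessment through week 33, and a footnote says safety measures are assessed similarly in both arms.

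**6. Possible size.** The protocol's 81% power is not in dispute, but it gives a scale. Take 12 per arm, d = 1.0, two-sided alpha 0.05 (sidedness assumed) and a baseline-adjusted SD of √(1 − 0.5²) = 0.866. Then z = (1.0 / 0.866) × √(12/2) − 1.96 = 0.87, giving 80.7%. This is a normal approximation; a t-based version gives 77.1%.

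The documents give no usage rate or drug effect. Assume 2 to 4 of 12 controls benefit from a drug worth 0.3 to 0.5 SD:

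- Low: 2/12 × 0.3 = 0.05 SD, so d = 0.95. Then z = (0.95 / 0.866) × 2.449 − 1.96 = 0.73, power 76.6%.
- High: 4/12 × 0.5 = 0.17 SD, so d = 0.83. Then z = (0.833 / 0.866) × 2.449 − 1.96 = 0.40, power about 65%.

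This takes control-arm use alone and fits drugs started after baseline best. For a drug already stable at baseline, part of the benefit is already in the baseline score.

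**The case against.** Several counter-arguments have force.

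- **The restriction is not confined to one arm everywhere.** A reader might infer from Section 6.3 that these drugs are restricted only in the psilocybin arm throughout the protocol. The Study Summary has an arm-neutral entry criterion, so at entry the defect is a contradiction and not a settled permission for controls to enroll on an antidepressant. This stands, and it is itself a reason to reconcile.
- **Withdrawal after baseline is not established.** A reader might infer that psilocybin-arm participants come off medication around week 3, between the two QIDS-SR-16 assessments. That follows from Sections 5.1 and 5.2 alone. The natural reading of Section 6.3 bars the drugs from week 1, although the treatment phase is not formally defined. What remains is a conflict over timing.
- **The comparison is still randomised.** Intention to treat validly compares the two strategies as delivered, so calling the comparison confounded would go too far. The loss is in attribution.
- **The illustrated shift is modest.** The standard error of the between-arm difference is √(2/12) = 0.41 SD, or 0.866 × 0.41 = 0.35 SD with baseline adjustment. Even 0.17 SD is under half of that, in a pilot meant to estimate effects and assess feasibility. This stands as a limit on magnitude.
- **An arm-specific restriction may have a safety reason.** It may, and nothing here disputes it.
- **Medication starts can be handled in the SAP.** Their analysis can. An SAP cannot resolve contradictory entry criteria or remove an asymmetry in the protocol's rules.

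**Conclusion.** The medication rules contradict each other on who they cover, on the date they count from, and on when the psilocybin arm must be drug-free. In Sections 5.1 and 5.2 they make eligibility depend on an allocation that comes later. During treatment they leave MBSR co-treatment open while restricting it in the psilocybin arm. A between-arm QIDS-SR-16 difference can therefore be read as a difference between strategies, but not as the effect of PAP alone.

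The size is unknown. Control-arm use alone would tend to hide a PAP benefit, by about 0.05 to 0.17 SD under the assumed usage and drug effects. Any stopping of medication in the psilocybin arm could move the contrast either way, so the net direction is unknown too. The contradiction and the asymmetry follow from the text; the size rests wholly on assumptions.

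**What to change.** 1. Reconcile the Study Summary criteria, Sections 5.1 and 5.2 (including the washout item) and Section 6.3. Which medication rule is clinically right is for the sponsor. Whatever it is, the entry criterion should be assessable before randomisation, with the same look-back for every candidate. The treatment phase in Section 6.3 should be defined so that its timing agrees with Section 5.
2. State whether the co-treatment rules are meant to differ by arm. If they are, give the reason and describe the depression contrast as a comparison of strategies.
3. From the concomitant-medication data already scheduled in Table 2, report psychotropic use, starts and stops by arm. Pre-specify one QIDS-SR-16 sensitivity analysis that handles them identically in both arms.

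The cost is an amendment to wording in a few places and a little extra analysis, with no new data collection. Depending on the rule the sponsor keeps, some candidates on medication may no longer be randomised.
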